### Study endpoints and assessments

*Primary outcome measure*: The percentage volume reduction of arm lymphedema (%) from baseline to 7 months.

*Secondary outcome measure*: Differences in circumference of the arm (cm), bodyweight (kg), patient sensation of heaviness (scale range: 0–10), patient sensation of tension (scale range: 0–10), and quality of life (EQ-5D-5 L-questionnaire).

Percentage volume reduction of arm lymphedema (%) from baseline to week 4.

Percentage volume reduction of arm lymphedema (%) from week 4 to week 7.

Length of treatment period until stable circumference of the arm (days).

All measurements are standardized and will be performed before randomization, after approximately 4 weeks and after 7 months (Table 1).

### Measurements

*Arm volume* (*ml*): Inverse Water Displacement Volumetry method [23] using Bravometer (Novuqare BV, PJ Horst, NL).

*Circumference* (cm) of the arm using measuring tape: Starting from the wrist, 5 circumference measures will be noted: wrist (1 measure) forearm (2 measures) and upper arm (2 measures) [24].

*Patient sensation of heaviness*: Scale ranging from 0–10 (0: no heaviness, 10: worst imaginable heaviness).

*Patient sensation of tension*: Scale ranging from 0–10 (0: no tension, 10: worst imaginable tension).

*Quality of life*: EQ-5D-5 L questionnaire (http://www.euroqol.org) [25].

### Sample size

The margin of equivalence, Δ, was defined as less than 12% points and the range -12% to +12% points thus is predefined as an acceptable range of imprecision (i.e., 95% confidence interval). This margin is based on clinically and statistically important differences as well as ethical criteria, cost and feasibility. In a two one-sided tests (TOST) analysis for additive equivalence of two-sample normal means with bounds -12 and 12 for the mean difference and a significance level of 0.05, assuming a null difference and a common standard deviation of 25%, a sample size of 76 patients with arm lymphedema per group is required to obtain a power of at least 0.8. It was decided to enroll 160 patients in the intention-to-treat (ITT) population. Secondarily to explore a potential difference between the groups, including 160 patients with a two-sided significance level of 0.05, assuming a common SD of 25%, a sample size of 80 per group has a power of 85.5% to detect a mean difference of 12% points.

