### Randomization and allocation concealment

After the baseline assessment, the participants will be randomly assigned to either treatment A or treatment B. The randomization sequence will be created using SAS (SAS 9.2) statistical software stratifying patients by center with a 1:1 allocation using random block sizes of 2, 4 and 6. The allocation sequence will be concealed from the researcher enrolling and assessing participants in sequentially numbered, opaque, sealed and stapled envelopes. Aluminum foil inside the envelope will be used to render the envelope impermeable to intense light.

The patients will be randomized (1:1) in one of the 2 groups:

1. Treatment-group A: standard treatment offered at the hospital containing skincare, manual lymphatic drainage, bandaging and guidance on physical activity.

2. Treatment-group B: standard treatment except for the manual lymphatic drainage. The treatment will include skin-care, bandaging and guidance on physical activity.

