### Statistical analyses

All data analyses will be carried out according to a pre-established analysis plan and all analyses will be done using SAS software (v. 9.2; SAS Institute Inc., Cary, NC, USA). All descriptive statistics and tests will be reported in accordance with the CONSORT statement for non-inferiority/equivalence trials [26], which is the recommendation of the “Enhancing the QUAlity and Transparency Of health Research” (EQUATOR) network [27]. In order to evaluate the empirical distributions of the continuous outcomes, visual inspection of the studentized residuals will be applied to evaluate whether the assumption of normality is reasonable.

Baseline demographic and clinical characteristics will be reported descriptively for all patients in the full analysis set.

The primary analyses will be based on the ‘full analysis set’ , referred to as the intention-to-treat (ITT) population. Missing data following baseline measurements will be replaced using a non-responder imputation (i.e., baseline observation carried forward) [28]. For assessments of change from baseline, analyses of covariance (ANCOVA) will be applied, with treatment assignment serving as the main factor and the baseline value as covariate. Point estimates and 95% confidence intervals (95% CIs) will be provided for the difference in adjusted mean change from baseline between the two treatment groups.

For the discrete (dichotomous) data, the estimate of the proportion of responders (with 95% CIs) within each treatment group, as well as the 95% CIs for the difference in response rates between treatment groups, will be presented.

Equivalence approach to analysis set: In order to demonstrate equivalence the entire 2-sided 95% CI lies within -12% points and +12% points. Thus, the per-protocol population, which includes the subset of patients from the ITT population who had no relevant protocol deviations, will be used to confirm the primary efficacy (equivalence) end point.

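### The trial is sized for equivalence tests at 0.05 (a 90% CI) but decided on a 95% CI, so power is about 71%, not at least 80%

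*Protocol article*

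**What the plan says.** The Sample size section of the protocol article bases the calculation on TOST for a comparison of two means, with the limits and level given as "bounds -12 and 12 for the mean difference and a significance level of 0.05". The true difference is taken to be zero, and the SD is 25 percentage points in both arms. From this it concludes that "a sample size of 76 patients with arm lymphedema per group is required to obtain a power of at least 0.8". The target is then rounded up to 160 patients. Allocation is 1:1 (Randomization and allocation concealment), so 80 per group are planned.

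The rule for declaring success is in the Statistical analyses section: "In order to demonstrate equivalence the entire 2-sided 95% CI lies within -12% points and +12% points". The Sample size section also links the range of ±12 points to a 95% interval. The primary analysis uses the intention-to-treat set, with missing values replaced by the baseline observation, and the per-protocol set is to confirm the equivalence result. A 90% interval is not mentioned anywhere.

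**The concern.** Two one-sided tests, each at level α, reject exactly when the two-sided 100(1 − 2α)% confidence interval lies inside the margin. TOST at 0.05 therefore goes with a 90% interval, and a 95% interval rule is TOST at 0.025. The article sizes the trial with the first and decides it with the second.

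Two things are at stake. First, the stated power does not belong to the decision that will be made, so the chance of an inconclusive trial is understated. In a trial whose main claim is that manual lymphatic drainage can be left out, failure to show equivalence could be misread as evidence that the drainage matters. Second, if the 90% interval lies inside ±12 and the 95% interval does not, the Sample size section supports a claim of equivalence and the Statistical analyses section forbids it. Settling that after the data are seen would be a post hoc choice of the success criterion for the primary endpoint.

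**Working it through.** **Inputs, all from the protocol article.** Margin m = 12 points, SD σ = 25 points, true difference 0, TOST level 0.05, 76 per group required, power at least 0.80, 160 enrolled (Sample size). Decision on the two-sided 95% CI (Statistical analyses).

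**Formulas.** With n per group, SE = σ√(2/n).

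- Normal approximation: power = 2Φ(m/SE − z₁₋α) − 1, where α is the level of each one-sided test.
- Exact: power = P(|d| + t₁₋α,₂ₙ₋₂ · s√(2/n) < m), where d is the observed difference and s the pooled SD, integrated over the distribution of s.

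**Step 1: reproduce the stated figure (α = 0.05 per side).** At n = 76, SE = 25√(2/76) = 4.056 and m/SE = 2.959. The approximation gives 2Φ(2.959 − 1.645) − 1 = 0.811. The exact power is 79.98% at n = 75 and 80.66% at n = 76, so 76 is the smallest n that reaches 80%. The stated figure is reproduced.

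**Step 2: apply the stated decision rule (α = 0.025 per side).**

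- n = 76: 2Φ(2.959 − 1.960) − 1 = 0.682; exact 67.3%.
- n = 80: SE = 25√(2/80) = 3.953 and m/SE = 3.036, so 2Φ(3.036 − 1.960) − 1 = 0.718; exact 71.0%.

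A simulation of 400,000 trials gave 67.4% and 71.1%.

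| n per group | Power, 90% CI rule | Power, 95% CI rule |
|---|---|---|
| 76 | 80.7% | 67.3% |
| 80 | 83.2% | 71.0% |

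**Step 3: could 0.05 have meant 0.025 per side?** No. At 0.025 per side the exact power is 79.9% at 92 and 80.5% at 93 per group. The answer would have been 93 per group (186 in total), not 76.

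**Step 4: what the rule demands of the data.** At 80 per group and an observed SD of 25, the half-width of the 95% CI is about 7.8 points, so the observed difference must lie within 12 − 7.8 = 4.2 points of zero. For a 90% CI the half-width is about 6.5 and the limit about 5.5 points.

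**Step 5: sensitivity at 80 per group, 95% CI rule.**

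- True difference (SD 25): 71% at 0, 65% at 2 points, 50% at 4 points.
- SD (true difference 0): 76% at 24, 81% at 23, 86% at 22.

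**Step 6: the per-protocol set.** The step from 152 (2 × 76) to 160 leaves room for 8/160 = 5% exclusions before the set falls below 76 per group. The article gives no exclusion rate. Taking 10% and 20% as illustrative assumptions, with SD still 25 and the exclusions equal in both arms:

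| Excluded | n per group | Power, 90% CI rule | Power, 95% CI rule |
|---|---|---|---|
| 10% | 72 | 77.8% | 63.2% |
| 20% | 64 | 70.9% | 53.7% |

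**The case against.** The strongest reply has four parts.

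- **The sum itself is correct.** True: 76 per group is right for TOST at 0.05. The fault is that this is not the test that decides the trial, so the power claim attached to it is wrong for the stated rule.
- **The planned size is 80 per group, not 76.** This also stands. The figure to lead with is 71%, and the failure chance is about 29%. The 67% figure applies to the 76 for which the article claims at least 80%.
- **The planned ANCOVA may recover power.** It may. If 25 is the unadjusted SD, a correlation of 0.3 between the baseline covariate and the outcome gives a residual SD of 25√(1 − 0.09) = 23.8 and power of 77%; a correlation of 0.4 gives 22.9 and 82%. Reaching 80% needs a residual SD of about 23.2, a variance reduction of about 14%. The article gives no correlation and claims no such gain in its power statement. Adjustment would also raise power under both rules without making them agree.
- **The 95% rule is the conservative one.** Correct: one-sided error is held at 2.5%, and a claim of equivalence under it is sound. The separate exploration of a difference (85.5% power for 12 points, which reproduces) would also help a reader interpret a failed equivalence test. Neither point makes the stated power true.

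**Conclusion.** The concern holds: the power statement is wrong as written for the decision rule in the same article. With SD 25, no true difference and an unadjusted comparison, power under the 95% CI rule is 67.3% at the stated 76 per group and 71.0% at the planned 80. The chance of missing equivalence between identical arms is thus about 29% at the planned size (33% at 76), against an implied 20% or less. Zero difference is the most favourable assumption; an SD reduced by ANCOVA would improve the figure by an amount the article does not allow one to calculate. At the same SD and true difference, the per-protocol confirmation has at most the same power. The error costs power and does not threaten the validity of a positive finding.

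**What to change.** Make the Sample size and Statistical analyses sections use one level before any unblinded data are seen, and carry it into the analysis plan.

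- **(a) Keep the 95% CI rule and correct the power statement (preferred).** Describe the calculation as TOST at one-sided 0.025, with power about 67% at 76 and 71% at 80 per group, and give per-protocol figures for a stated exclusion rate. If a gain from ANCOVA is claimed, state the correlation assumed. The cost is wording and a less favourable power figure; the roughly 29% chance of failure remains.
- **(b) Keep TOST at 0.05 and declare equivalence on the 90% CI**, reporting the 95% CI alongside. Power is then 83.2% at 80 per group. No patients are added, but the success rule is relaxed and its one-sided error rises from 2.5% to 5%. This is more debatable and would need a justification fixed before unblinding.
- **(c) If 80% power under the 95% CI rule is wanted**, about 93 per group are needed: 186 in total, or 26 more than planned.

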### Randomization and allocation concealment

After the baseline assessment, the participants will be randomly assigned to either treatment A or treatment B. The randomization sequence will be created using SAS (SAS 9.2) statistical software stratifying patients by center with a 1:1 allocation using random block sizes of 2, 4 and 6. The allocation sequence will be concealed from the researcher enrolling and assessing participants in sequentially numbered, opaque, sealed and stapled envelopes. Aluminum foil inside the envelope will be used to render the envelope impermeable to intense light.

The patients will be randomized (1:1) in one of the 2 groups:

1. Treatment-group A: standard treatment offered at the hospital containing skincare, manual lymphatic drainage, bandaging and guidance on physical activity.

2. Treatment-group B: standard treatment except for the manual lymphatic drainage. The treatment will include skin-care, bandaging and guidance on physical activity.

### Statistical analyses

All data analyses will be carried out according to a pre-established analysis plan and all analyses will be done using SAS software (v. 9.2; SAS Institute Inc., Cary, NC, USA). All descriptive statistics and tests will be reported in accordance with the CONSORT statement for non-inferiority/equivalence trials [26], which is the recommendation of the “Enhancing the QUAlity and Transparency Of health Research” (EQUATOR) network [27]. In order to evaluate the empirical distributions of the continuous outcomes, visual inspection of the studentized residuals will be applied to evaluate whether the assumption of normality is reasonable.

Baseline demographic and clinical characteristics will be reported descriptively for all patients in the full analysis set.

The primary analyses will be based on the ‘full analysis set’ , referred to as the intention-to-treat (ITT) population. Missing data following baseline measurements will be replaced using a non-responder imputation (i.e., baseline observation carried forward) [28]. For assessments of change from baseline, analyses of covariance (ANCOVA) will be applied, with treatment assignment serving as the main factor and the baseline value as covariate. Point estimates and 95% confidence intervals (95% CIs) will be provided for the difference in adjusted mean change from baseline between the two treatment groups.

For the discrete (dichotomous) data, the estimate of the proportion of responders (with 95% CIs) within each treatment group, as well as the 95% CIs for the difference in response rates between treatment groups, will be presented.

Equivalence approach to analysis set: In order to demonstrate equivalence the entire 2-sided 95% CI lies within -12% points and +12% points. Thus, the per-protocol population, which includes the subset of patients from the ITT population who had no relevant protocol deviations, will be used to confirm the primary efficacy (equivalence) end point.

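### Baseline observation carried forward, the primary ITT rule for missing data, favours equivalence when dropout is similar between arms; its effect on power depends on mean reduction and dropout balance

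*Protocol article*

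**What the plan says.** All references are to the Protocol article.

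- **Endpoint** (Study endpoints and assessments): "The percentage volume reduction of arm lymphedema (%) from baseline to 7 months". The 4-week equivalent is a secondary outcome, "Percentage volume reduction of arm lymphedema (%) from baseline to week 4", and Table 1 schedules arm volume at baseline, 4 weeks and 7 months.
- **Primary set** (Statistical analyses): the full analysis set, "referred to as the intention-to-treat (ITT) population".
- **Missing data** (Statistical analyses): "Missing data following baseline measurements will be replaced using a non-responder imputation (i.e., baseline observation carried forward".
- **Decision rule** (Statistical analyses): "In order to demonstrate equivalence the entire 2-sided 95% CI lies within -12% points and +12% points". The per-protocol population "will be used to confirm the primary efficacy (equivalence) end point".
- **Planning values** (Sample size): "bounds -12 and 12 for the mean difference and a significance level of 0.05", "assuming a null difference and a common standard deviation of 25" percentage points, 76 per group required and 160 enrolled. No dropout rate and no expected mean reduction are given.

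**The concern.** Counting a missing patient as a non-responder is cautious when the aim is to show that treatments differ. Here the aim is to show that they do not. Replacing the 7-month volume by the baseline volume gives exactly 0% reduction, whichever arm the patient is in. Identical values in both arms pull the two means together, which supports the trial's own hypothesis.

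The risk is an ITT interval that falls inside the margin although the true difference lies on it. The rule also ignores the week 4 volume of any patient who attended that visit and then missed month 7. The imputation rule is stated in the article, so this is not a detail left to an analysis plan.

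**Working it through.** **The plan's own figures.** Exact TOST power (margin 12, SD 25, true difference 0, 0.05 per one-sided test) is 0.7998 at 75 and 0.8066 at 76 per group, so 76 is reproduced. Superiority power for 12 points at 80 per group is 0.8548, matching the stated 85.5%.

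**Inputs.** From the article: 80 per arm (160/2), SD 25, margin ±12, 95% CI. Assumed, because the article gives neither: mean reductions μA and μB, and missing fractions dA and dB. Missingness is taken as unrelated to outcome, and the baseline covariate in the ANCOVA is not modelled.

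**Formulas.** After carry-forward:

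- arm mean = (1-d)μ
- arm variance = (1-d)(25² + dμ²)
- D = (1-dA)μA - (1-dB)μB
- SE = √[(VA + VB)/80]
- b = 12 - 1.975 × SE (t critical value, 158 df)
- P(equivalence declared) = Φ((b-D)/SE) - Φ((-b-D)/SE)

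**Example: 40% v 28%, 10% missing per arm.** D = 0.9 × 12 = 10.8. VA = 0.9(625 + 0.1 × 1600) = 706.5. VB = 0.9(625 + 0.1 × 784) = 633.06. SE = √(1339.56/80) = 4.092. b = 3.918. P = Φ(-1.682) - Φ(-3.597) = 4.6%.

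**False equivalence at a true difference of 12 (40% v 28%):**

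| Missing A / B | D | SE | P (formula) |
|---|---|---|---|
| 0 / 0 | 12.0 | 3.953 | 2.4% |
| 5% / 5% | 11.4 | 4.032 | 3.4% |
| 10% / 10% | 10.8 | 4.092 | 4.6% |
| 20% / 20% | 9.6 | 4.155 | 8.0% |
| 15% / 5% | 7.4 | 4.133 | 19% |
| 5% / 15% | 14.2 | 4.033 | 0.6% |

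Simulations of 40,000 trials per setting agree: 2.4 to 2.5% with nothing missing, 3.3 to 3.5% at 5%, 4.5 to 4.8% at 10%, 7.9 to 8.2% at 20%, 19 to 20% at 15% v 5%, and 0.6% at 5% v 15%. Analysing observed values only, with the same missingness, stays at 2.4 to 2.6%. The change therefore comes from the imputation rule and not from the missing data as such.

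**Unequal dropout with truly equal arms.** The spurious difference is μ(dA - dB) in size. At μ = 40 and 15% v 5% it is 40 × 0.10 = 4 points, and power is 44%, against 63% with observed values only.

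**Power with equal dropout and no true difference.** With complete data, power under the 95% CI rule is 71%. That it is below 80% comes from sizing at 0.05 per side and then using a 95% CI, which is a separate matter.

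- Carry-forward has a larger SE than complete data only if (1-d)(625 + dμ²) > 625, that is μ > 25/√(1-d): 26.4% at d = 10% and 28.0% at d = 20%.
- It has a larger SE than observed values only if (1-d)(625 + dμ²) > 625/(1-d), that is μ² > 625[1/(1-d)² - 1]/d: 38.3% at d = 10% and 41.9% at d = 20%.
- At 10% missing, power with carry-forward is 74% (μ = 20), 62% (μ = 40) or 43% (μ = 60), against 63% with observed values only.

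**The case against.** **The per-protocol confirmation.** This is the strongest counter-argument. If that set excludes patients without 7-month data and both analyses must succeed, simulated false equivalence (40% v 28%) is 2.1% at 10% per arm, 2.1% at 20% per arm and 2.3% at 15% v 5%. A reader might take the ITT figures as the error rate of the whole trial. The article does not support that, because it plans this second analysis. It is still only a partial answer. The article does not say how the per-protocol set treats a missing 7-month value, and requiring both analyses costs power: the joint power cannot exceed the lower of the two, 62% v 63% at μ = 40 and 10% missing.

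**Dropout may be small.** Moving from 76 to 80 per group leaves room for 4/80 = 5% loss, where false equivalence is only about 3.5%. That stands, although the article never states 5% as an expectation.

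**Return to baseline may be realistic.** The Background describes a chronic condition that tends to worsen untreated, so some patients who stop may drift back. The calculations take missingness as unrelated to outcome, so they do not show that a missing-at-random (MAR) analysis is better when dropout depends on outcome. This supports keeping carry-forward as a sensitivity analysis.

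**Stronger readings to avoid.**

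- *Carry-forward always costs power or widens the SD.* It does not; with smaller reductions it raises power through artificial zeros.
- *The longer group A sessions will cause unequal dropout.* The article gives no dropout rates or direction. Active treatment lasts about 4 weeks, the endpoint is at 7 months, and the sleeve advice does not differ by arm.
- *The rule invents relapse after week 4.* Taken literally, a patient 40% reduced at week 4 and missing at month 7 would score (60 - 100)/60 = -67%. The article does not spell out how the rule enters changes from week 4, and those outcomes are secondary.
- *Sensitivity analyses are missing.* They are commonly left to the analysis plan.

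**Conclusion.** The point holds for the primary ITT analysis. With similar dropout, carry-forward biases the comparison towards equivalence: on the assumed 40% v 28%, false equivalence goes from about 2.5% to about 3.5%, 4.6% and 8% at 5%, 10% and 20% missing. For equal dropout the result is not peculiar to those means; centring the two arms anywhere from 20% to 50% gives 4.3 to 4.8% at 10% missing and 6.6 to 9.0% at 20%. With unequal dropout the error can go far above or below nominal, depending on which arm loses more. The effect on power has no fixed sign.

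All sizes rest on assumed dropout and mean reductions, on missingness unrelated to outcome, and on an analysis without the baseline covariate. The direction under equal dropout follows from the factor (1-d) alone. Because a per-protocol confirmation is planned, this is a worthwhile, inexpensive improvement rather than a flaw shown to invalidate the trial.

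**What to change.** Before unblinding, make the primary ITT analysis a likelihood-based repeated-measures model, or multiple imputation within arm, using baseline volume, the week 4 volume already scheduled in Table 1 and all observed 7-month data. Keep baseline observation carried forward as a sensitivity analysis, and add one that shifts the imputed values against equivalence by the margin. State whether the per-protocol set excludes patients without a 7-month measurement, and whether both analyses must meet the ±12 rule.

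In simulation at 10% to 20% missing (assumed week 4 to month 7 correlation 0.7, missingness unrelated to outcome), a repeated-measures analysis held false equivalence at 2.0% to 2.7% for 40% v 28%. For equal arms at 40% its power was 66% at 10% missing and 61% at 20%.

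The cost is revised wording and modest programming, with no new data or visits. The downside is reliance on a MAR assumption, which the two sensitivity analyses probe.

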## Background

Breast cancer is the most common type of cancer in women and in 2011, 4607 women in Denmark were diagnosed with breast cancer [1]. One of the well-known complications of breast cancer treatment is secondary lymphedema; an accumulation of protein-rich interstitial fluid due to the insufficient capacity of the lymphatic system. Axillary lymph-node dissection and subsequent radiation therapy are the most common causes of arm lymphedema [2,3]. The incidence of lymphedema as a sequelae to breast cancer treatment ranges from 6-50%, depending on the surgical procedure in the axilla and the type of the radiation therapy [2,4]. The reported prevalence relies among other things on the definition of lymphedema and which techniques are used to measure it [5]. Lymphedema occurs most often within the first year following the treatment [6,7] and 77% of the patients develop lymphedema within the first three years post-surgery [8].

Lymphedema is a chronic condition and when untreated, the risk of worsening of the lymphedema over time in terms of volume and stage of tissue fibrosis increases [9-11]. In addition to the cosmetic deformities, lymphedema causes impaired physical mobility, mental discomfort, social isolation [12], reduced quality of life [12,13] and higher incidence of erysipelas [12,14].

Physical therapy treatment of patients with lymphedema is based on the principles of ‘Complete Decongestive Therapy’ (CDT). CDT consists of the following components; skin care, manual lymphatic drainage, bandaging and exercises. Traditionally, the bandages used in CDT have been short-stretch bandages. In Denmark, the most commonly used manual lymphatic drainage method is described by Földi [15-17]. The treatment is based on manual lymphatic drainage 4–5 times weekly and each treatment takes 30–45 minutes. However, standardization between different treatment locations and among treating physiotherapists does not exist.

The scientific evidence regarding what type of treatment or combination of treatments is most effective is sparse. Studies [2,3,7,14] have focused on time-consuming manual lymphatic drainage, but the scientific evidence is not consistent [18-20]. The lack of robust evidence may be a contributory cause to the variation of available treatment options among different treatment locations and among treating physiotherapists.

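### Randomization is stratified by center but the stated ANCOVA has no center term; to the extent that centers differ, the CI that decides equivalence is conservatively too wide and loses power

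*Protocol article*

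**What the plan says.** Protocol article, Randomization and allocation concealment: the sequence is generated "stratifying patients by center with a 1:1 allocation using random block sizes of 2, 4 and 6". There are three hospitals, and the Intervention section expects about equal recruitment from each.

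Protocol article, Statistical analyses: for change from baseline, "analyses of covariance (ANCOVA) will be applied, with treatment assignment serving as the main factor and the baseline value as covariate". The reported result is described as follows: "Point estimates and 95% confidence intervals (95% CIs) will be provided for the difference in adjusted mean change from baseline between the two treatment groups". The decision rule is: "In order to demonstrate equivalence the entire 2-sided 95% CI lies within -12% points and +12% points". The per-protocol set is then used to confirm the result. No section of the article puts center into any analysis.

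**The concern.** The design treats center as a factor worth controlling, and the written analysis then ignores it. Permuted blocks within center keep the two arms nearly equal in number at each hospital, so a hospital with generally better or worse outcomes shifts both arms alike and drops out of the treatment difference. A model without center does not know this. It counts the spread between hospitals as residual noise and reports a standard error that is larger than the true one.

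In an equivalence trial the whole CI must fit inside the margin, so any unneeded width lowers the chance of confirming equivalence that is really there. What is at stake is efficiency. The error runs in the safe direction for a false claim of equivalence.

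**Working it through.** **Inputs from the protocol article**

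- Margin and test level (Sample size): "bounds -12 and 12 for the mean difference and a significance level of 0.05".
- True difference and SD, in percentage points (Sample size): "assuming a null difference and a common standard deviation of 25".
- Sample size: "a sample size of 76 patients with arm lymphedema per group is required to obtain a power of at least 0.8"; 160 enrolled, so 80 per arm.
- Decision rule (Statistical analyses): two-sided 95% CI within ±12, which is TOST at 0.025 per side.

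**Assumption, not in the documents.** Let c be the share of the outcome variance due to center. SD 25 is taken as the total SD, including differences between centers. The range for c is 0% to 15%.

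**Step 1: reproduce the plan's figures.** Exact two-sample t power for TOST at 0.05 per side, with margin 12, SD 25 and true difference 0, is 0.7998 at 75 per group and 0.807 at 76. So 76 per group is correct as stated. Superiority power for a 12-point difference at 80 per group is 0.855, which matches the stated 85.5%.

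**Step 2: CI width.**

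- Half-width without center: t × 25 × √(2/80) = 1.975 × 3.953 = 7.81.
- Half-width with center: t × 25√(1−c) × √(2/80). At c = 10% this is 1.975 × 23.72 × 0.1581 = 7.41.
- Ratio: 1/√(1−c), apart from a negligible change in t. At c = 10% this is 1/√0.90 = 1.054.

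**Step 3: coverage without center.** The true standard error is 25√(1−c) × √(2/80), but the model uses 25 × √(2/80). Coverage is about 2Φ(1.96/√(1−c)) − 1. At c = 10% this is 2Φ(2.066) − 1 = 96.1%.

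**Step 4: power at true difference 0.** For a given estimated standard error, the CI falls inside ±12 with probability 2Φ((12 − t × estimated SE)/true SE) − 1. This is averaged over the chi-square distribution of the estimated variance. The true SE uses 25√(1−c) in both analyses. The estimated SE centers on SD 25 without center and on 25√(1−c) with center.

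| Center share c | Half-width without / with center | CI too wide by | Coverage without center | Power without center | Power with center |
|---|---|---|---|---|---|
| 0% | 7.81 / 7.81 | 0% | 95.0% | 71.0% | 70.9% |
| 2% | 7.81 / 7.73 | 1.0% | 95.2% | 71.4% | 72.3% |
| 5% | 7.81 / 7.61 | 2.6% | 95.6% | 72.2% | 74.4% |
| 10% | 7.81 / 7.41 | 5.4% | 96.1% | 73.5% | 77.8% |
| 15% | 7.81 / 7.20 | 8.5% | 96.6% | 74.8% | 81.1% |

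At c = 0% the two powers differ by less than 0.1 point.

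**Step 5: risk of false equivalence.** At a true difference of 12, the chance of wrongly declaring equivalence without center is about Φ(−1.96/√(1−c)): 2.2% at c = 5% and 1.9% at c = 10%, against the nominal 2.5%. Simulated trials with three centers of 53 or 54 patients and permuted blocks of 2, 4 and 6 gave 2.3% and 1.8%. In the same simulations at true difference 0, coverage without center was 95.5% at c = 5% and 95.9% at c = 10%, against 95.0% and 95.2% with center.

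**The case against.** Four points can be made against the concern.

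1. **The center effect may be nil.** No between-center variance is given, and at a zero center effect the CI is the same width with or without center. This stands, so the point can only be conditional and the range has to start at 0%.

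2. **The Background does not show a center effect in this trial.** A reader might take its remark that "standardization between different treatment locations and among treating physiotherapists does not exist" as the plan's own admission that centers will differ. It describes routine Danish practice and is part of the case for doing the trial. The Methods set one regimen for all three hospitals: the same components, the same bandage, one drainage method, fixed session lengths twice a week, standardized measurement and assessors who do not treat. This also stands. A center effect remains possible, since each hospital has its own physiotherapists and the length of treatment varies by patient, but the documents neither state nor quantify one.

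3. **It is not a validity error.** A reader might infer that a model that ignores the stratification factor makes the equivalence claim unsafe. Step 5 shows the opposite: false equivalence falls below the nominal rate. The loss is efficiency only.

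4. **An analysis plan that is not shown may add center.** The article refers to a pre-established plan, and its model sentence covers all change-from-baseline outcomes in general terms. That is possible. But the article does more than leave the model open: it names the terms, and the stratification factor is not among them. Mention of another document does not change what this one specifies.

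**Conclusion.** The mismatch between stratified randomization and the written ANCOVA is real. Its effect is a CI that is too wide only to the extent that centers differ in 7-month percentage volume reduction. For center shares of 2% to 10% the CI is 1.0% to 5.4% too wide, and power is lower by 0.9 points (72.3 − 71.4) to 4.3 points (77.8 − 73.5). At 0% nothing is lost. These sizes rest on SD 25, 80 per arm, a true difference of 0, near-equal arms within centers, and an assumed center share. This is a minor but nearly free improvement, and no threat to the validity of an equivalence claim.

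A reader might also infer that adding center restores the planned 80% power. It does not do so by itself. The 76 per group was computed at TOST level 0.05, which corresponds to a 90% CI, while the decision uses a 95% CI. Under that rule power is about 67% at 76 per group and 71% at 80, and 93 per group would be needed for 80%. With center in the model, power is still 77.8% at a center share of 10% and passes 80% only somewhere between 10% and 15%, a level that nothing in the documents supports. That shortfall is a separate issue and needs its own resolution.

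**What to change.** Add center (three levels, fixed effect) to the ANCOVA for the primary outcome and the continuous secondary outcomes, in both the ITT and per-protocol sets, and say so in the Statistical analyses text. If the unpublished analysis plan already includes center, bring the article's wording into line with it. Make the change before outcome data are seen, so that in a borderline result it cannot look like a choice made after the fact.

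The cost is 2 degrees of freedom out of 157 (160 patients less intercept, treatment and baseline), leaving 155. No further patients, visits or data are needed, and if centers do not differ the loss of power is below 0.1 point.
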